**Investigation**

Baseline investigations like complete blood count, liver function test, renal function test, fasting blood sugar, LDH, D-dimer, CRP, serum ferritin, BNP, Trop-I, CPK, PT/INR, procalcitonin - will be done at admission. RFT, LFT, CPK, Trop-I, BNP, D-dimer, CRP, serum ferritin will be repeated on the 5^th^ day and at the time of discharge.

**Randomization**

Enrollment eligibility will be accessed by the person admitting patients. Before assigning groups to eligible individuals to participate in the study, written informed consent will be taken by the medical officer posted in the covid centre. Block randomization technique will be used to assign patients to the standard care (control) or current intervention (intervention group). We will use a block size of four study participants during the randomization process. Allocation to intervention or control group will be done by the treating team in the covid centre. Allocation concealment is done by the treatment team.

**Blinding**

This will be an open-label study. In this study, all participants are aware of participating in the study and enroll in the study after consent. The participants will be aware of the group assigned. Patients receive aspirin, atorvastatin, nicorandil in the intervention group(A) over and above the standard of care, and patients in the control group (B) will receive standard of care only. The health care personal, data collecting officials, and those who evaluate the outcome are aware of the grouping of patients.

**Sample size**

A total sample size of 396 was calculated assuming alpha error=0.05, power 80%, death in the control group of 20% (5), the death rate in the treatment group =15%, a superiority margin of 5%, and a nonresponse rate (loss to follow up) of 10% using sample size calculator <http://riskcalc.org/samplesize/>.

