**Method and Materials**

**Objectives**

To test whether triple therapy with aspirin, atorvastatin, and nicorandil is superior to usual care in SARS-CoV-2 infected patients in improving outcome.

To find out the safety of triple therapy in SARS-CoV-2 infected patients.

**Study Design**: Single-centre, prospective, two-arm parallel design, open-label randomized control superiority trial.

**Place of Study**: The study will be conducted at the covid centre of [name] Government Medical College Tanda Kangra, Himachal Pradesh India, converted into a dedicated COVID-19 management centre since August 2020.

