**Statistical Analysis:**

Descriptive statistics will be used to summarize variables. All primary and additional endpoints will be analysed both on intention-to –treat (ITT) basis and on a per-protocol (PP) basis for the study. The ITT population set consists of all patients who have provided informed consent and have been randomized to a treatment group. All patients will be analysed according to the assigned treatment group, regardless of the treatment received.

The PP population set will consist of all patients who have provided informed consent and have been randomized to a treatment group, and who have received only the assigned study treatment, without any major protocol deviation. Participants who do not receive a study treatment, or who receive any treatment other than the study treatment to which they were randomized, will be excluded from the PP population. All participants will be analysed according to the treatment that they received. A supportive analysis of the primary endpoint and all secondary clinical endpoints will also be conducted in the PP population. Wilcoxon rank-sum test will be used for nonnormal distribution. Time-to-event will be compared using the Kaplan-Meier curve and log-rank test. The Cox proportional hazards model will be used to calculate the hazards ratio and 95% Confidence Interval. Safety outcomes will be compared between the groups using Chi-square or Fisher’s exact test.

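### The total of 396 is reproduced only by adding the 5% margin to the 5-point benefit, as in a non-inferiority calculation; power for superiority at 20% versus 15% is about 24%, not 80%

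*Protocol*

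**What the plan says.** The Objectives section sets a superiority question: "To test whether triple therapy with aspirin, atorvastatin, and nicorandil is superior to usual care". The study design entry also calls the trial a superiority trial, and the primary outcome is in-hospital mortality.

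The Sample size section gives one justification for the trial's size: "A total sample size of 396 was calculated assuming alpha error=0.05, power 80%, death in the control group of 20% (5" (the final 5 is a reference number), then "the death rate in the treatment group =15%, a superiority margin of 5" per cent, and a 10% allowance for loss to follow-up. It cites an online calculator. It gives no formula and does not say whether alpha is one-sided or two-sided.

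The Statistical Analysis section names Kaplan-Meier curves and the log-rank test, and adds: "The Cox proportional hazards model will be used to calculate the hazards ratio and 95% Confidence Interval". It tests nothing against a margin.

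**The concern.** A superiority trial that seeks a fall in mortality from 20% to 15% normally needs far more than 396 patients, so the claim of 80% power looked implausible. The margin is also odd. A margin to be exceeded makes a superiority test harder, and here it equals the whole assumed benefit. If it enters the formula with the opposite sign, it doubles the apparent effect and cuts the sample size to a small fraction of what is needed.

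This is the only power statement for the primary outcome. If it is wrong, a null result could be presented as coming from an adequately powered trial when the trial had little chance of detecting the benefit it was designed around.

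**Working it through.** **Inputs (Sample size section):** control deaths 20%; treatment deaths 15%; alpha 0.05, sidedness not stated; power 80%; margin 5 points; loss 10%. Equal allocation is assumed: the protocol has two arms and blocks of four but states no ratio.

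**1. Reproducing 396.** Variance term: 0.20 × 0.80 + 0.15 × 0.85 = 0.16 + 0.1275 = 0.2875. With the margin added to the benefit and one-sided alpha 0.05:

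n per arm = (z₀.₉₅ + z₀.₈₀)² × 0.2875 / (0.05 + 0.05)² = (1.645 + 0.842)² × 0.2875 / 0.01 = 177.7, so 178.

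Total 2 × 178 = 356, and 356 / 0.9 = 395.6, so 396. The match is exact. As a check, 178 per arm gives 80.0% power to show that treatment is no more than 5 points worse when it is truly 5 points better. The same formula at one-sided 0.025 gives 226 per arm, and 452 / 0.9 = 502.2, which is not 396.

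**2. Superiority without a margin.** Pooled rate 0.175, so the null variance term is 2 × 0.175 × 0.825 = 0.28875.

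n per arm = (z_α √0.28875 + z₀.₈₀ √0.2875)² / 0.05²

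| Test | n per arm | Evaluable | With 10% loss, equal arms |
|---|---|---|---|
| Two-sided 5% | 905.4, so 906 | 1,812 | 2,014 |
| One-sided 5% | 714 | 1,428 | 1,588 |

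A continuity correction raises the totals to 2,100 and 1,674.

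**3. The margin taken literally.** If the benefit must exceed 5 points, the assumed benefit (20% − 15% = 5 points) lies on the null boundary. Power then equals alpha at any sample size, and no finite number reaches 80%.

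**4. Power at the planned size.** Power = Φ[(0.05 − z_α √(0.28875/n)) / √(0.2875/n)]. For n = 178, two-sided: (0.05 − 1.96 × 0.04028) / 0.04019 = −0.72, and Φ(−0.72) = 23.6%.

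| n per arm | Two-sided 5% | One-sided 5% |
|---|---|---|
| 178 (356 evaluable) | 23.6% | 34.3% |
| 198 (all 396) | 25.7% | 36.8% |

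Exact two-sided calculation for the chi-square test gives 23.6% and 26.1%.

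**5. Time-to-event version.** Hazard ratio ≈ ln 0.85 / ln 0.80 = 0.73. Expected deaths are 356 × 0.175 = 62.3 or 396 × 0.175 = 69.3. The Schoenfeld approximation gives 24% and 26% (two-sided), so the log-rank or Cox analysis does not recover the power.

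**6. What the planned size can do.** At two-sided 5%, 80% power requires treatment mortality of about 9.5% (178 per arm) or 10.0% (198 per arm), roughly a halving. The 95% confidence interval half-width for the risk difference is 1.96 × √(0.2875/178) = 7.9 points, or 7.5 points with 198 per arm. Both exceed the 5-point effect sought.

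**The case against.** The strongest reply is that the formula is inferred. The protocol names only a calculator, and a superiority-margin formula with the sign reversed for an adverse outcome, (0.15 − 0.20) − 0.05 = −0.10, gives the same number. That stands: the documents cannot show which route was taken. Either way the margin has been added to the effect, and the power figures use only the stated rates, alpha and sample size.

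Second, the 24% assumes a two-sided test, while one-sided 0.05 is the alpha that reproduces 396. The planned 95% interval fits a two-sided 5% test but does not fix the alpha of the primary comparison. In addition, the Withdrawal section does not count a patient as lost if vital status is known before discharge, so for in-hospital death nearly all 396 may be evaluable. Both points are fair and widen the range to 24–26% two-sided and 34–37% one-sided. None of these values approaches 80%.

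Third, a separate statistical analysis plan may exist. It could not make this calculation correct, because the claim is made in the protocol.

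**Conclusion.** The concern holds. The stated 80% power does not exist for the stated question. With 20% versus 15% mortality and equal arms, the trial has 24–26% power at two-sided 5% and would miss a real reduction of that size about three times in four. At one-sided 5% it would still miss it nearly two times in three. The size needed for 80% power is about five times the planned total two-sided (2,014 / 396 = 5.1) and about four times one-sided (1,588 / 396 = 4.0).

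The route to 396 is an inference from an exact numerical match. The shortfall in power does not depend on it. How readers would treat a null result is a judgement, but the protocol as written would support the wrong reading.

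**What to change.** Remove the superiority margin from the Sample size section and restate the section for a two-sided 5% test of no difference. Suggested content: 396 randomised patients, 356 evaluable after 10% loss, give about 24% power for 20% versus 15% (about 26% if all are evaluable), and 80% power only if treatment mortality is about 9.5% (10.0% if all are evaluable). State the 1:1 allocation and the formula.

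It would also help to say in advance that a non-significant result is inconclusive for a 5-point difference, and to report the risk difference with its 95% confidence interval. This is advisable but is not needed to correct the error.

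The cost is protocol wording and a much less favourable power statement; no extra patients are needed. If the sponsor wants to keep the claim of 80% power for 20% versus 15%, the alternative is a trial of about 2,014 patients.

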**Outcome and measurement**

Data collection is done by the specially trained nursing officers of the hospital. Patients’ demographic data and clinical data including age, sex, comorbidities, baseline vital information, saturation, treatment received, type of oxygen support, baseline and follow-up investigation information, outcome, and safety endpoint information will be recorded on structured proforma.

**Primary outcomes**

The primary outcome will be in-hospital mortality.

**Secondary outcomes**

The secondary outcomes will be any progression to ARDS, shock, acute kidney injury, impaired consciousness, and length of hospital stay, length of mechanical ventilation (invasive plus non-invasive). Changes in serum markers (CRP, D –dimer, S ferritin) will be other secondary outcomes.

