**4.Examination**

|  | At admission |
| --- | --- |
| SBP |  |
| DBP |  |
| Respiratory rate |  |
| Pulse rate |  |
| Pulmonary rales |  |

5.**Spo2**

| At admission | | At discharge |
| --- | --- | --- |
| Without oxygen support | Oxygen support (face mask) |  |
|  |  |  |
| Duration of days with spo2<95% | |  |

6.**Treatment**

|  | Yes/no |
| --- | --- |
| Hydroxychloroquine |  |
| Ivermectin |  |
| Doxycyclin |  |
| Azithromycin |  |
| Remdisivir |  |
| Tocilizumab |  |
| Vit D |  |
| Vit C |  |
| Corticosteroid |  |
| LMWH |  |
| Proton pump inhibitor |  |
| Antibiotic |  |

7.**Oxygen therapy**

|  | START | | END | | Duration(days/hour |
| --- | --- | --- | --- | --- | --- |
|  | DATE | TIME (am/pm) | DATE | TIME(am/pm) |  |
| Nasal prongs |  |  |  |  |  |
| Facemask |  |  |  |  |  |
| NRM |  |  |  |  |  |
| HFNC alone |  |  |  |  |  |
| HFNC plus face mask |  |  |  |  |  |
| HFNC plus NRM |  |  |  |  |  |
| CPAP |  |  |  |  |  |
| Invasive ventilation |  |  |  |  |  |
| The total duration of oxygen therapy |  | | | |  |

8.**Investigation**

|  | At admission | 5^th^ day |  |
| --- | --- | --- | --- |
| RBS |  |  |  |
| HB |  |  |  |
| TLC |  |  |  |
| ESR |  |  |  |
| Platelet count |  |  |  |
| Total bilirubin |  |  |  |
| Direct bilirubin |  |  |  |
| AST/ALT |  |  |  |
| ALP |  |  |  |
| LDH |  |  |  |
| S. Creatinine |  |  |  |
| S. FERRITIN |  |  |  |
| Prothrombin time |  |  |  |
| D-dimer |  |  |  |
| CRP |  |  |  |
| BNP |  |  |  |
| Procalcitonin |  |  |  |
| Troponin I |  |  |  |
| CPK |  |  |  |

9.**Primary endpoint**

|  | Yes/no |
| --- | --- |
| In-hospital mortality |  |
| Duration of mechanical ventilation |  |
| Length of hospital stay | (duration) |
| ARDS |  |
| Shock |  |
| Acute kidney injury |  |
| Impaired consciousness |  |
| Delirium |  |
| Stupor |  |
| Coma |  |

10.**Safety endpoints**

|  | Yes/no |
| --- | --- |
| Hepatotoxicity |  |
| Major bleeding |  |
| Minor bleeding |  |
| Proximal muscle weakness |  |
| Myalgia |  |

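### The four progression outcomes leave out death, so a patient who dies without a recorded complication counts as a non-event; with unequal mortality this can add up to 5 points of apparent excess to the intervention arm

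*Protocol*

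**What the plan says.** The Protocol's Secondary outcomes section lists four progression events: "The secondary outcomes will be any progression to ARDS, shock, acute kidney injury, impaired consciousness". In-hospital death is the separate primary outcome and is a component of none of them.

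Item 9 of the Appendix-I Proforma gives each event, for example "Acute kidney injury", its own row under a Yes/no heading. In-hospital mortality is another row of the same table. No row has an onset date, and no entry covers death before the event.

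The Exclusion criteria remove patients with ARDS, shock, acute renal failure or altered mental status at presentation, so all four events are new events after entry. Under Statistical Analysis, the intention-to-treat set is everyone randomised, so patients who die stay in the denominator. The same section says "Time-to-event will be compared using the Kaplan-Meier curve and log-rank test", without naming the outcomes meant or how death is handled.

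The Sample size section assumes "death in the control group of 20"% and "the death rate in the treatment group =15"%.

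**The concern.** For each complication, two very different patients share the answer No: one who went home well, and one who died before the complication occurred or was recorded. That would matter little if deaths were rare or equal between arms. The trial is planned on neither assumption.

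If treatment prevents deaths, some patients who would have died without the complication live long enough to develop it. They move from No to Yes, and only in the intervention arm. Part of a survival benefit can then appear as excess complications. The stated objective is superiority in improving outcome, and the proforma lists these events beside mortality under its primary-endpoint heading, so they are likely to be read as evidence of efficacy.

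For kidney injury the schedule adds to this. The Investigation section repeats renal function only on day 5 and at discharge, so a patient who dies before day 5 has no scheduled post-baseline renal test.

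**Working it through.** **Inputs from the protocol.** Total 396; mortality 20% control and 15% treatment; 10% loss to follow-up. Equal allocation is assumed from two arms and blocks of four, giving 198 per arm.

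**The plan's own figure.** 396 is reproduced by a one-sided 5% test with 80% power in which the 5-point margin is added to the 5-point expected difference:

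n per arm = (1.645 + 0.842)² × (0.20×0.80 + 0.15×0.85) / 0.10² ≈ 178; 2 × 178 / 0.9 = 395.6, rounded up to 396.

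Whether that formula suits a superiority trial is a separate matter. Here it supplies only the numbers per arm: 198 randomised, 178 after loss.

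**Expected deaths.** 198 × 0.20 = 39.6 and 198 × 0.15 = 29.7, together 69.3 of 396 (17.5%). This counts all deaths. The artefact concerns only deaths without the complication, which the protocol does not size.

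**Size of the artefact.** Averted deaths are 20 − 15 = 5 points. Let f be the share of them that would have been complication-free and are followed by the complication once averted. The artefact is 5 × f points.

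The standard error of a risk difference with 178 per arm is √(2p(1−p)/178): 3.18 points at p = 0.10 and 4.24 at p = 0.20. This range of p is assumed; the Introduction gives 15% for ARDS.

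| f (assumed) | Artefact, points | Patients per 198 | In standard errors |
|---|---|---|---|
| 0.05 | 0.25 | 0.5 | 0.06–0.08 |
| 0.25 | 1.25 | 2.5 | 0.3–0.4 |
| 0.50 | 2.5 | 5 | 0.6–0.8 |
| 1 (ceiling) | 5 | 10 | 1.2–1.6 |

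f needs two things to happen: the averted death would have been complication-free, and the survivor then develops the complication. Illustrative products are 0.2 × 0.25 = 0.05, 0.5 × 0.5 = 0.25 and 0.71 × 0.71 ≈ 0.5.

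**Net difference.** Let q be the share of deaths without the complication and r the complication rate in patients whose death is averted. Then treatment minus control = 5 × [r − (1 − q)] points. This equals 5 × (f − g), where g is the share of averted deaths in which a complication is averted too. The g part is genuine benefit; only the f part is artefact.

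**Illustration.** Assume a 20% complication rate in the 80% who survive in either arm, q = 1 and r = 0.5:

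| | Control | Treatment |
|---|---|---|
| Complication | 0.80×20 = 16.0% | 16.0 + 5×0.5 = 18.5% |
| Death without complication | 20.0% | 15.0% |
| Neither | 64.0% | 66.5% |
| Complication or death | 36.0% | 33.5% |

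The complication alone shows a 2.5-point excess on treatment, although fewer patients have a bad outcome. With q = 0.5 and r = 0.5 the complication rates are equal, at 26% in each arm. With q = 0.25 and r = 0.5 they are 31% and 29.75%, which favours treatment.

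**The case against.** The strongest objection is that handling death as a competing event is usually left to the statistical analysis plan, which is not shown, and that the Secondary outcomes section says nothing false. The first part stands to this extent: the lack of a competing-risk rule would not be a finding on its own. But the outcome definitions and the data form belong to the protocol, and they fix the problem in place. With no onset dates for these events, a later plan could not build a cumulative-incidence analysis from this form.

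A reader might infer that the protocol tells staff to tick No for these patients or treats them as good outcomes. No sentence says so; it follows from the form's two options. Because mortality is in the same table, patients who died without the complication can be identified. That limits the harm and makes the fix cheap.

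A reader might also infer that these deaths will be censored in a Kaplan-Meier analysis. The protocol does not assign that method to these outcomes, and the form could not supply the event times, so this is only a possibility to guard against.

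On size, it is fair to say that most deaths in patients admitted with pneumonia may pass through ARDS or shock, which would make f small for those two. This is an assumption, but a reasonable one. Even at the ceiling (16% versus 21%, 198 per arm), a two-sided 5% test would be significant only about 25% of the time.

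Finally, replacing all four outcomes with death composites would have a real cost: organ-specific information would be lost, and a mortality benefit would read as a complication benefit. That objection stands, and the fix adds to the outcomes instead of replacing them.

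**Conclusion.** The point holds in a limited form. As defined and recorded, each complication counts a death without that complication as a non-event, and the planned mortality difference makes this unequal between arms. The artefact works against a treatment that saves lives. It cannot exceed 5 points and is plausibly 0.25 to 2.5 points. It is likely smallest for ARDS and shock, and larger for acute kidney injury and impaired consciousness. The ceiling rests on the protocol's 20% and 15%; the plausible range and the ordering rest on assumed values of f, which the protocol does not give.

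Two stronger readings are not supported. The roughly 70 expected deaths are not all affected, because an unknown share will have had the complication recorded first. Nor does it follow that treatment will look harmful or that these outcomes are useless for the objective: the net difference can go either way, and mortality is reported alongside. Only secondary outcomes are affected, so this is a low-cost improvement and not a threat to the primary comparison.

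**What to change.** In Secondary outcomes, keep ARDS, shock, acute kidney injury and impaired consciousness as listed. For each:

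- add complication or in-hospital death, compared as a proportion of all randomised patients;
- report by arm a three-row table of complication, death without complication, and neither;
- state that deaths are not to be censored if any time-to-event method is used for these outcomes. Such a method would also need onset dates added to the proforma.

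The first two items need only wording, since both components are already on the form. No extra patients and no change of treatment are involved. The downside is that the four composites share their deaths with the primary outcome and are less organ-specific. In the illustration the composite favours treatment by 2.5 points with no direct effect on the complication. The text should therefore say that the composites are read with the three-row table and are not evidence of an effect on a particular organ.

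### The CRP, D-dimer and ferritin outcomes have no fixed time point: a change to discharge does not exist for patients who die, and a baseline-adjusted day-5 comparison is more precise at almost no cost

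*Protocol*

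**What the plan says.** Four sections of the protocol bear on this point.

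- Secondary outcomes: "Changes in serum markers (CRP, D –dimer, S ferritin) will be other secondary outcomes". No time point and no scale (raw, percentage or log) is given.
- Investigation: all three markers are measured at admission. The later samples are placed as follows: "will be repeated on the 5^th^ day and at the time of discharge".
- Statistical Analysis: "Wilcoxon rank-sum test will be used for nonnormal distribution". This is a general rule that names no variable. The section mentions no transformation and no baseline adjustment. It promises an intention-to-treat analysis of every endpoint, with that set made up of all consenting randomised patients. It gives no rule for a marker value that is absent because the patient died.
- Primary outcomes: "The primary outcome will be in-hospital mortality". The event that removes the discharge sample is therefore the primary outcome itself.

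The laboratory table of the proforma labels an admission and a day-5 column. Its third column carries no label in the text available, so nothing is inferred from it.

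**The concern.** Two post-baseline samples compete to define the change. Three markers at two times give six possible comparisons. The trial is open-label and the Blinding section says that those who evaluate outcomes know the allocation, so the choice of time point should not stay open.

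The two samples are not equally good. The day-5 sample falls at the same time after admission for everyone who has it. The discharge sample exists only for patients discharged alive, assuming that no equivalent sample is taken at death, since none is described. It also falls on a different day for each patient. Length of stay is itself a secondary outcome, so treatment may move the sampling day. An arm comparison on the discharge value is thus conditioned on survival and on time to discharge, and it leaves out randomised patients whom the intention-to-treat set includes.

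There is also avoidable loss of precision. The admission value is to be measured in every patient, yet the protocol names no method that adjusts for it.

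**Working it through.** **Inputs from the protocol (Sample size).** Total 396; alpha 0.05; power 80%; death rates 20% (control) and 15% (treatment); margin 5%; loss to follow-up 10%. Equal arms (198 each) are assumed from the blocks of four. The protocol gives no correlation, spread or effect size for the markers, so those below are assumptions.

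**The plan's own figure.** The 396 is reproduced with a one-sided alpha and the margin added to the difference:

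- per arm: (0.20 × 0.80 + 0.15 × 0.85) × (1.645 + 0.842)² / 0.10² = 177.7, so 178;
- total: 2 × 178 = 356, and 356 / 0.9 = 395.6, so 396.

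It serves here only to supply 198 randomised and 178 evaluable per arm. The protocol states no figure for the markers.

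**Patients without a discharge value because of death.**

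- control: 198 × 0.20 = 39.6;
- treatment: 198 × 0.15 = 29.7;
- together: 69.3, and 69.3 / 396 = 17.5%.

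**Size of the bias from death alone.** Survivor selection was simulated at 20% against 15% mortality with no treatment effect on the marker, a correlation of 0.5 between the two measurements, and a correlation of 0.3, 0.5 or 0.7 between the later marker and the risk of death. The treatment-minus-control difference among survivors, in log-SD units, was:

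| Marker–death correlation | Log change | Adjusted for baseline |
|---|---|---|
| 0.3 | 0.012 | 0.017 |
| 0.5 | 0.014 | 0.024 |
| 0.7 | 0.029 | 0.041 |

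The bias is small, and baseline adjustment does not remove it. The bias from differing discharge days cannot be computed, because the protocol gives neither the distribution of discharge days nor the time course of the markers.

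**Precision.** Let s² be the variance of the log marker, equal at both times, and r the correlation between admission and day 5.

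- unadjusted log change: 2s²(1 − r);
- log day-5 value adjusted for log admission value: s²(1 − r²);
- ratio: (1 − r²) / [2(1 − r)] = (1 + r) / 2.

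For r = 0.3, 0.5, 0.7 the ratio is 0.65, 0.75, 0.85, which is 35%, 25% or 15% less variance with the same patients.

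That formula does not cover a rank test on skewed raw changes, so power was simulated: lognormal markers, log-SD 1, log means 4 at admission and 3.3 afterwards in controls, a treatment shift of 0.25 SD, 178 per arm, 2,000 runs.

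| Analysis | r = 0.3 | r = 0.5 | r = 0.7 |
|---|---|---|---|
| Wilcoxon on raw change | 23% | 30% | 39% |
| Wilcoxon on log change | 50% | 63% | 85% |
| Log model adjusted for baseline | 69% | 79% | 92% |

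Type I error was 4% to 6% for all three.

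**The case against.** The strongest reply is that the protocol does not say what a critic may read into it. A reader might infer that raw changes will be compared by Wilcoxon test and that the discharge value enters the comparison. Neither is stated: the scale is left open, the Wilcoxon sentence is general, and the Investigation section is a sampling schedule that also covers tests outside the marker outcomes. This stands, so the point is that the outcome is left open and that the only fitting method named is unadjusted.

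Second, the model, the transformation and sensitivity analyses are commonly left to a statistical analysis plan, and none is shown here. A rank test on changes in a randomised trial is also valid, as the type I errors confirm, and it does use the baseline, by subtraction, though less efficiently. This stands too: the adjusted model is offered as a gain in precision, not as the correction of an error. It does not answer the missing time point, which is part of the outcome's definition, nor the intention-to-treat promise that a change to discharge cannot meet.

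Third, a reader might conclude that the discharge comparison is seriously biased, or that everyone sampled at discharge has recovered by definition. The document supports neither. It gives no discharge criteria, and the simulated bias from death alone is 0.01 to 0.04 SD.

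Fourth, day 5 has gaps of its own. Patients who die or leave before day 5 lack that sample, and their number is not given. This is accepted and is dealt with in the remedy.

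**Conclusion.** The concern holds in a limited form. The marker outcomes lack a time point. One of the two candidate times cannot be computed for about 69 of 396 patients (17.5%) at the planned death rates with equal arms, split unequally at about 40 against 30 if treatment works as assumed. It also falls on an outcome-dependent day. A change to discharge therefore cannot be analysed by intention to treat as the Statistical Analysis section promises.

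The resulting bias should not be overstated. From death alone it is probably small under the assumed model; from differing discharge days it is unknown. Day 5 is less biased rather than unbiased, and any reduction in bias comes from the time point, not from the adjustment.

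The precision gain is the firmer benefit: variance falls to 0.65 to 0.85 of that of an unadjusted log change for r between 0.3 and 0.7. The direction was the same at every r tried; the size rests on assumed r and, for the power figures, on assumed skewness and effect. The point concerns secondary laboratory outcomes only and leaves the mortality outcome untouched. It should be settled before the data are analysed.

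**What to change.** 1. State in Secondary outcomes that the marker outcomes are assessed at day 5.
2. Compare log(day-5 marker) between arms with log(admission marker) as covariate, and report a ratio of geometric means with 95% confidence interval. This still answers the question about change: with the admission value in the model, the arm effect is the same whether log day-5 value or log change is the response.
3. Add a sensitivity rank analysis that gives deaths before day 5 the worst rank and treats discharges before day 5 by a stated rule, for example using the discharge sample as the last value.
4. Report discharge values descriptively, with the number of patients who have none.

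The cost is wording only, since every sample is already scheduled in the Investigation section. What is given up is a formal test of the discharge values. The main day-5 model remains limited to patients sampled on day 5, which is why the third item is needed.
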